### Microlearning Email Campaign

Once randomly assigned, participants will receive their designated microlearning campaign. The microlearning campaign is intended to reinforce learnings from the primary e-learning content and is customized to each group. Emails will be automated to be sent twice weekly.

### Poststudy Surveys

Poststudy surveys will be released to each participant at T2 (8 weeks) and remain open for 2 weeks. Poststudy surveys will not be released to participants who did not complete the prestudy surveys. Participants in the intervention group will be invited to participate in a follow-up qualitative interview with the research team.

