**Methods:**

This study is a 2-arm, pilot, feasibility, randomized controlled trial. A total of 125 family or friend care partners for a person living with dementia—who are residing in Canada, aged 16+ years, and comfortable using the internet and email—will be recruited using coinvestigator networks and Facebook digital marketing advertisements. Participants will be randomly assigned to either the intervention group (receiving the dementia web- and email-based educational intervention) or the control group (receiving an alternate topic e-learning lesson and emails) and will have 8 weeks to complete baseline surveys and the assigned e-learning. After 8 weeks, participants will have 2 weeks to complete poststudy surveys. This protocol will be repeated with a second cohort of 100 care partners recruited from a paid panel service based on learnings from initial feasibility results.

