#### Randomization and Intervention Assignment

Following account creation, the research platform will automatically randomly assign participants either to the intervention group or the control group using stratified permuted block randomization with variable block sizes of 4, 6, and 8 (randomly arranged) in a ratio of 1:1, based on care partner type (care partner to a spouse, care partner to a parent, and care partner to someone other than a spouse or parent), and level of education (high school equivalent or less, some college or university, and college or university or graduate degree).

Once a participant is randomly assigned to either the intervention or control group, an application programming interface (API) will be used to assign each participant to the matching microlearning email campaign and course in the learning management system. Participants will receive an account verification email and once verified can begin to access their assigned surveys and web-based course (prestudy surveys, e-learning lesson[s], and poststudy surveys).

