#### e-Learning Content

After completion of the prestudy surveys, the intervention group will receive access to 10 selected e-learning lessons from iGeriCare (Figure 1). The control group will receive access to a single e-learning lesson on “Promoting Brain Health.” Each group will be provided access to the other group’s e-learning content at the conclusion of the study. Specific lesson titles and outlines for the intervention and control groups are displayed in Table 1.

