### Knowledge, Self-Efficacy, and Burden

Linear mixed models will be used to assess the relationship between group assignment and score for each of the outcomes: the DKAS and its subdomains (causes and characteristics, communication and behavior, care considerations, and risks and health promotion), the RSCSE and its subdomains (obtaining respite, managing disruptive behaviors, and controlling upsetting thoughts), and the ZBI. All models will include the 2 stratification factors, education level (high school equivalent or less, some college or university, and college or university or graduate degree) and care partner type (care partner to a spouse, care partner to a parent, and care partner to someone other than a spouse or parent). Group assignment will be included as the primary independent variable of interest with interaction from time to determine how the relationship between outcome score and group assignment will change from baseline to follow-up. Potential effect modifiers, including age (categorized as <44 years, 45-64, and ≥65 years), gender, education level, stage of dementia (mild [early-stage] dementia, moderate [middle-stage] dementia, severe [late-stage] dementia, or “I don’t know”), and length of time as a care partner (less than 3 months, more than 3 months but less than 1 year, more than 1 year but less than 2 years, more than 2 years but less than 5 years, or more than 5 years), will be explored in relation to group assignment. These variables will be retained in the model if the likelihood ratio test indicates a significant difference between the nested model and the full model (*P*<.05). If they are not significant modifiers of the group-outcome relationship, then they will be investigated as effect modifiers with respect to time. An intention-to-treat analysis will also be performed and include all individuals as per group assignment. A per-protocol analysis will also be performed. Correlations between the number of lessons in the intervention completed and the DKAS score will be analyzed.

We will also look for inverse correlations between the DKAS and ZBI scores, as well as between the RSCSE and ZBI scores. Analyses will be performed using an α level of .05 and 2-sided tests. All analyses will be conducted using RStudio software (Posit).

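### Withholding the T2 surveys from randomised participants who did not complete T1 means that the stated intention-to-treat analysis cannot include everyone randomised

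*Protocol article*

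**What the plan says.** The order of events can be read from the Protocol article.

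- **Randomisation** (Randomization and Intervention Assignment): "Following account creation, the research platform will automatically randomly assign participants either to the intervention group or the control group". The prestudy surveys sit inside the assigned course, which opens after assignment and account verification.
- **Emails** (Microlearning Email Campaign): "Once randomly assigned, participants will receive their designated microlearning campaign". The emails differ by arm and go out twice a week.
- **Window for T1** (Abstract, Methods): participants "will have 8 weeks to complete baseline surveys and the assigned e-learning".
- **Lessons** (e-Learning Content): "After completion of the prestudy surveys, the intervention group will receive access to 10 selected e-learning lessons from iGeriCare". The control lesson is opened in the same way.
- **T2** (Poststudy Surveys): "Poststudy surveys will not be released to participants who did not complete the prestudy surveys".
- **Analysis** (Knowledge, Self-Efficacy, and Burden): linear mixed models with group, time and their interaction, for a population that is not named. Then: "An intention-to-treat analysis will also be performed and include all individuals as per group assignment". And: "A per-protocol analysis will also be performed".

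**The concern.** Completing T1 is something a participant does, or fails to do, after being assigned to an arm. Making T2 conditional on it is an exclusion after randomisation that is built into the trial procedures. The plan still describes its intention-to-treat analysis as covering everyone assigned.

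Two things are at stake. First, the label would claim a property that the data do not have: the analysed set would be chosen by behaviour after allocation, and randomisation does not protect the comparison within such a set. Second, the lost outcomes cannot be recovered. Someone who received arm-specific emails for 8 weeks without completing T1 might have answered T2, but was never offered it. An analysis plan can specify how to handle missing values, but it cannot restore surveys that were not released.

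The point also matters beyond these two runs, because the pilot is meant to inform a larger trial, which could inherit the same release rule.

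**Working it through.** **1. Order of events.** Account creation, then randomisation, then arm-specific emails and access to the arm-specific course. T1 is taken inside that course within the 8-week window, then the lessons open, then T2. T1 completion therefore follows randomisation and can coincide with arm-specific exposure.

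**2. What each type of participant gives the mixed model.**

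| Participant | T1 score | T2 score | Contribution |
|---|---|---|---|
| Completed T1, answered T2 | yes | yes | both times |
| Completed T1, did not answer T2 | yes | no | baseline only |
| Stopped partway through T1 | possibly, for some scales | barred | baseline only, at most |
| Never started T1 | no | barred | none |

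A simulated mixed model confirms the last row: with 125 randomised and 25 lacking both scores, the model used 125 − 25 = 100 participants. Under the stated rule and model, the last two rows cannot supply a follow-up outcome.

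**3. How many.** Inputs: 125 randomised in run 1 (61 + 64) and 100 in run 2 (53 + 47), from Initial Cohort Participants and Second Cohort Participants. The T1 non-completion proportion q is not in the text, and the flow diagrams are not shown. The up-to-30% dropout under Sample Size is not split by stage. So q is an assumption, taken from 5% to 20%. Number barred from T2 = N × q.

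| q (assumed) | Run 1, N = 125 | Run 2, N = 100 |
|---|---|---|
| 5% | 6.25, about 6 | 5 |
| 10% | 12.5, about 13 | 10 |
| 20% | 25 | 20 |

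**4. What this does to the planned effect.** Suppose non-completers would score D lower than completers at both times. The completers' mean in an arm then lies q × D above the mean of all randomised in that arm, at T1 and at T2 alike. With D = 0.5 SD and q = 10% in one arm and 20% in the other, the lifts are 0.05 and 0.10 SD. A comparison at T2 alone would shift by 0.10 − 0.05 = 0.05 SD.

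The planned effect is the group-by-time interaction, a difference in change. Within each arm the lift cancels: (T2 mean + qD) − (T1 mean + qD) = T2 mean − T1 mean. The shift in the planned effect is 0. For bias, T1 completion must depend on arm, and it must also be related to change in outcome rather than only to its level. The documents contain no figure for either, so no size is derived.

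**The case against.** The strongest case on the other side has four parts.

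- **No evidence of differential loss.** The prestudy surveys are identical in both arms, and the lessons stay locked until T1 is done. The only arm-specific content described before T1 is the emails. This stands: differential loss is possible, not shown.
- **The model can use partial data.** A person who stopped partway may have a T1 score, and imputation could formally include everyone. This stands in part. Partial responders add baseline only, and imputing both times from arm and two stratification factors adds almost no outcome information.
- **Analysis sets and missing data belong in the analysis plan.** That document is not shown, so a missing ranking of populations or imputation method is no fault in itself. This stands for those details. It does not answer the contradiction between the release rule and the promise to include everyone, because both are stated in the article.
- **The consequence is limited.** The primary outcome is feasibility, T1 non-completion bears on the planned completion and attrition measures, blinded analysis is planned, and the study is described as not powered to fully assess effectiveness. This stands and lowers the severity.

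A reader might also infer from the word used to introduce it that intention-to-treat has been demoted to an additional analysis. The text does not support that: the per-protocol analysis is introduced in the same way, and no other population is placed above either.

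**Conclusion.** The release rule and the intention-to-treat statement cannot both hold as written. T2 is withheld because of an event after randomisation, so the stated mixed model cannot include everyone as assigned. This conclusion rests only on the sequence in the text.

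The number affected is unknown. About 6 to 25 of 125 and 5 to 20 of 100 follow from an assumed 5% to 20% non-completion, and the true counts should be available to the investigators.

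A reader might infer that the treatment effect is biased by some fraction of an SD, such as the 0.05 SD in the T2-only illustration. The documents do not support this: a pure level difference cancels in the group-by-time effect, and nothing in the text shows that completion depends on arm or is related to change.

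Severity: this should be fixed, but it does not undermine the trial. It affects a secondary outcome of a pilot not powered for effectiveness.

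**What to change.** **Runs 1 and 2 (data collection has ended):**

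- Replace the statement that everyone is included with a true description of the set, for example randomised participants with at least one outcome score, analysed as assigned.
- Report T1 non-completion by arm for each run.
- State that the as-randomised analysis is the main one and per-protocol is supportive, if the analysis plan does not already do so. This is worth fixing before results are seen, because run 1 is already known to contain many participants who did not engage as intended.
- Add a sensitivity analysis over all 125 and all 100 randomised, with arm-specific shifts applied to the imputed outcomes over a stated range. Say plainly that imputation from the stratification factors adds little information. The analysis shows how far the unobserved participants would have to differ to change the reading of the result; it does not recover the lost data.

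Cost: a few sentences of wording, one set of counts and one extra analysis.

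**The larger trial that this pilot informs:** complete T1 before randomisation, or release T2 to every randomised participant whether or not T1 was completed. Cost: a change in the order of platform steps, or one release rule in the learning management system. Releasing T2 to everyone brings the loss imposed by design to zero, though ordinary non-response will remain.

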### Outcome Measures

Our primary outcome is to evaluate the feasibility of implementation, including study methods, of the iGeriCare e-learning content within a clinical trial context. The secondary outcome is to determine the effectiveness of the intervention on knowledge, self-efficacy, and care partner burden.

### Feasibility of Implementation of the Intervention

We will examine intervention adherence as measured by lesson completion data and email open rates, level of technical and participant support required from the research team including tracking and sending reminders, participant satisfaction survey ratings, and exit interview data from a sample of participants from the intervention group.

### Feasibility of the Study Methods

Study methods will also be evaluated. We will examine recruitment rate as measured by participants per day, participant acceptability of the intervention and surveys as measured by completion and attrition rates, time to complete the intervention and surveys, level of engagement and exposure to the intervention (including potential “fast trackers” moving through the intervention at a high speed), survey data, and exit interview data.

### Clinical Effectiveness Outcomes

#### Knowledge

Knowledge will be measured through the Dementia Knowledge Assessment Scale (DKAS; reliability α=.85; ωh=.87; overall scale) [29]. The DKAS consists of 25 items on different aspects of dementia that could be answered with “True,” “Probably True,” “False,” “Probably False,” or “I don’t know.”

#### Self-Efficacy

Self-efficacy will be measured through the Revised Scale for Caregiving Self-Efficacy (RSCSE; reliability α≥.80) [30]. The RSCSE contains 15 items within 3 subscales (self-efficacy for obtaining respite, responding to disruptive patient behaviors, and controlling upsetting thoughts about caregiving).

#### Burden

Burden will be measured through the Zarit Burden Interview (ZBI; reliability α=.92) [31]. The ZBI contains 22 items. Each item on the interview is a statement that the caregiver is asked to endorse using a 5-point Likert scale. Response options range from 0 (“Never”) to 4 (“Nearly Always”).

### Qualitative Interviews

A sample of 10 consenting participants from the intervention arm will also be invited to participate in a 10-minute semistructured telephone interview looking for their impressions about their experience, user acceptance, barriers, and facilitators related to the educational tools and the intervention. This will allow the participants to have the freedom to express their experience, as opposed to having closed-ended questions. While we anticipate interviewing approximately 10 participants from the intervention group, we will also look for saturation of themes or feedback to determine when to terminate interviews. Interview items will be based on a participatory knowledge translation framework and mixed methods informed by the Consolidated Framework for Implementation Research (CFIR) to evaluate factors that could influence implementation effectiveness. The qualitative interview guide can be viewed in Multimedia Appendix 1.

### Data Analysis

Blinded data analysis will be performed upon data collection for both cohorts. The CONSORT (Consolidated Standards of Reporting Trials) extension for randomized pilot and feasibility trials as well as CONSORT-EHEALTH will be used for final reporting [32-34].

### Participant Characteristics

Differences in participant demographics between groups will be assessed using unpaired 2-tailed *t* tests. Both stratification factors, care partner type (care partner to a spouse, care partner to a parent, and care partner to someone other than a spouse or parent) and level of education (high school equivalent or less, some college or university, and college or university or graduate degree), will be included in all models. In addition, age, sex, education, stage of dementia, and length of time as a care partner will be looked at as possible effect modifiers of the relationship between the group and the outcomes, and timepoint and the outcomes.

### Feasibility of Implementation and Study Methods

Quantitative feasibility-related outcomes (eg, email open rates and participant satisfaction survey ratings) will be compared between groups using unpaired 2-tailed *t* tests. Qualitative feedback from postcourse surveys and semistructured interviews will be coded, themed, and analyzed using a generic qualitative approach [35]. Qualitative content analysis will focus on the identification of barriers and facilitators to the adoption of iGeriCare e-learning, participant perceptions of the intervention, whether they felt it met their needs, and other experiences with the intervention, outcome measures, and study protocol.

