**Figure 2 figure2:**
[figure not shown]
Study flow diagram for run 1.

Preliminary results showed a substantial number of participants who did not engage with the protocol as initially intended. A number of participants were identified as not having completed the protocol as intended, as demonstrated by “fast-tracking” through the e-learning (ie, clicking next without allowing time for reading or listening to content) or by repeatedly clicking “I don’t know” on prestudy or poststudy surveys.

Following this, a decision was made to recruit an additional cohort of participants (n=100) using learnings gained from the initial recruitment cohort concerns. A paid panel service, AskingCanadians, was engaged to assist with recruitment. AskingCanadians is a reputable paid panel service that was able to specifically target family and friend care partners of people living with dementia.

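### The only quantitative analysis stated for the primary feasibility outcomes is a between-arm t test, which cannot show feasibility; t tests are also fixed for categorical demographics

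*Protocol article*

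**What the plan says.** Outcome Measures sets the aim: "Our primary outcome is to evaluate the feasibility of implementation, including study methods". Research Questions puts it as whether the intervention is feasible for participants.

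The measures are listed in two sections:
- Feasibility of Implementation of the Intervention: "We will examine intervention adherence as measured by lesson completion data and email open rates", with support required, satisfaction ratings and exit interviews.
- Feasibility of the Study Methods: "We will examine recruitment rate as measured by participants per day", and "participant acceptability of the intervention and surveys as measured by completion and attrition rates", with time to complete, engagement (including fast trackers), survey data and exit interviews.

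Under Data Analysis, the subsection Feasibility of Implementation and Study Methods gives the quantitative method: "Quantitative feasibility-related outcomes (eg, email open rates and participant satisfaction survey ratings) will be compared between groups", using unpaired two-tailed t tests. The rest of that subsection is qualitative.

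For baseline, Participant Characteristics says: "Differences in participant demographics between groups will be assessed using unpaired 2-tailed" t tests. It names no other method and makes no exception for categorical items.

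**The concern.** The question and the analysis do not match. Feasibility asks about a level: how many enrol per day, how many stay, how many complete the lessons. The planned test asks about a difference between arms. Two arms that both do badly, and two that both do well, give the same null result. A significant difference does not help either, because the arms carry different workloads: "the intervention group will receive access to 10 selected e-learning lessons from iGeriCare", while the control group gets one lesson on another topic.

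The study exists to plan a larger trial. If its primary result is a set of between-arm P values, the planners lack the rates, and the uncertainty around them, that they need.

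The demographic t tests are a smaller fault of the same kind. The characteristics that the article defines are categories, and a t test on a nominal variable depends on the numbers chosen as codes.

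**Working it through.** There is no planned feasibility figure to reproduce: the article states no feasibility threshold and no precision target. The illustrations use 40 per arm, the final size expected in Sample Size. The completion rates and category counts are assumed.

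**1. Does the t test respond to the level of feasibility?** Score completion 0/1 and compare the arms.
- 8/40 v 8/40 (20%): t = 0, P = 1.00
- 20/40 v 20/40 (50%): t = 0, P = 1.00
- 36/40 v 36/40 (90%): t = 0, P = 1.00

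Now take 36/40 v 28/40 (90% v 70%). The sample variances are 0.9 × 0.1 × 40/39 = 0.0923 and 0.7 × 0.3 × 40/39 = 0.2154, with mean 0.1538. The standard error is √(0.1538 × 2/40) = 0.0877, so t = 0.20/0.0877 = 2.28 and P = 0.025. The test reports a difference where both rates are high, and none where both are 20%.

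**2. Are the arms comparable on lesson completion?** Summing the durations in Table 1:
- Intervention minimum: 10+20+20+15+15+20+25+35+10+10 = 180 minutes
- Intervention maximum: 15+25+25+20+20+25+30+40+15+12 = 227 minutes
- Control: 25-30 minutes

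The intervention workload is between 180/30 = 6 and 227/25 = 9.1 times that of control. A difference in completion mixes feasibility with workload.

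**3. Does every measure have an arm?** No. Recruitment precedes randomisation. From the Results dates, run 1 took 27 days (6 September to 2 October 2022, inclusive), so 125/27 = 4.6 per day. Run 2 took 16 days (12 to 27 June 2023), so 100/16 = 6.3 per day. These are rates by run; there is nothing for a two-arm t test to compare.

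**4. What would estimation give?** Exact (Clopper-Pearson) 95% limits are the 2.5% point of Beta(x, n−x+1) and the 97.5% point of Beta(x+1, n−x). For the run 2 intervention arm (n = 53), at assumed results:

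| Completed | Rate | Exact 95% interval |
|---|---|---|
| 16/53 | 30% | 18.3-44.3% |
| 26/53 | 49% | 35.1-63.2% |
| 37/53 | 70% | 55.7-81.7% |
| 48/53 | 91% | 79.3-96.9% |

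For all of run 2, 70/100 would give 60.0-78.8%. Statements of this kind separate a poor result from a good one.

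**5. Demographics.** Participant Characteristics and Knowledge, Self-Efficacy, and Burden define care partner type (three nominal levels), education (three levels), gender, age in bands, stage of dementia (with a don't-know option) and banded length of caring. Take an illustrative three-level nominal variable with counts 18/4/18 v 6/28/6.
- Coded 1, 2, 3: both means are 2.0, so t = 0 and P = 1.00.
- Coded 2, 1, 3: the means are 94/40 = 2.35 and 58/40 = 1.45. The variances are 17.1/39 = 0.438 and 21.9/39 = 0.562, with mean 0.500. The standard error is √(0.500 × 2/40) = 0.158, so t = 0.90/0.158 = 5.69 and P = 2.1e-7.
- Chi-square, free of coding: the expected counts are 12, 16 and 12 per arm; 4 × 6²/12 + 2 × 12²/16 = 12 + 18 = 30.0 on 2 df, P = 3.1e-7.

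The same data give opposite t-test answers under two arbitrary numberings.

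**The case against.** **What the other side can say.** The article adds a between-group comparison and does not say that it replaces descriptive rates. Recruitment per day, completion and attrition are themselves rates, and Future Results promises a report on overall feasibility. The qualitative analysis bears on acceptability. The two named examples, email opening and satisfaction, exist in both arms, and per-participant values can be compared by t test. Thresholds may sit in a fuller document. The demographic P values drive nothing, since the stratification factors enter all models anyway, and age might be collected in years.

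**What of it stands.** Missing thresholds are not a fault of this article, and the qualitative work is not in question. The demographic point is minor. But the t test is a stated method, not an omission, and it is the only quantitative one given for the primary outcome. That rates may also be reported does not make the named analysis answer the question. If age is continuous, a t test is computable for age and remains unsuitable for the nominal items.

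**Stronger readings that the article does not support.**
- A reader might infer that adherence will be overstated, because run 1 participants were found "clicking next without allowing time for reading or listening to content". The article does not say that such lessons count as completed, and it already plans to examine time to complete and fast trackers.
- A reader might take 70% retention as the plan's own criterion, from the dropout allowance of up to 30%. That is a recruitment assumption, and the same paragraph expects 80 of 125, which is 64%.
- A minimum time per lesson as the test of completion would need timing of each lesson, which the article does not confirm is recorded.

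**Conclusion.** The point holds for the quantitative analysis as stated. A between-arm t test cannot answer the feasibility question: it returns P = 1.00 at 20%, 50% and 90% alike. It has no meaning for recruitment rate, and for lesson completion it compares workloads that differ six- to nine-fold. Extending the t test to lesson completion assumes that the two named outcomes are only examples, as the wording indicates. The mismatch with the research question does not depend on that assumption.

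For demographics, t tests do not fit the categorical characteristics the article defines. The consequence is limited to an uninformative baseline table.

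The point does not rest on any success threshold, nor on a claim that descriptive rates will go unreported. It should be corrected before the feasibility results are reported; the data already collected are not affected.

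**What to change.** **Feasibility of Implementation and Study Methods (Data Analysis).** State that the primary feasibility analysis is estimation, with 95% intervals (exact for proportions):
- recruitment per day, by run;
- retention and survey completion, by arm and run;
- lesson completion, email opening and satisfaction in the intervention arm.

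Use all randomised participants as the denominator for retention and completion. Report lesson completion beside the time-to-complete and fast-tracker data already planned. Keep any between-arm comparison of these measures as descriptive only.

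**Participant Characteristics.** Summarise demographics by arm as counts and percentages, with mean and SD for any continuous item, and drop the t tests.

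**Cost.** A change of analysis wording, with no new data. There will be no between-arm P values for feasibility.
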